## Abstract

**Background:**

Although available evidence relating to its effectiveness is weak, acupuncture is used as an alternative therapy for stress urinary incontinence. We report a protocol of a randomized controlled trial using electroacupuncture (the passing of a weak current between inserted acupuncture needles) to treat women with pure stress urinary incontinence.

**Methods/Design:**

This is a large-scale multicenter subject-blinded randomized controlled trial. A total of 500 women with pure stress urinary incontinence will be randomly assigned to two groups: a treatment group and a control group. The treatment group will receive electroacupuncture with deep needling at acupuncture points BL33 and BL35. The control group will receive sham electroacupuncture with non-penetrating needling at sham locations for the acupuncture points of BL33 and BL35. Participants will be given three sessions a week for 6 weeks. A 24-week-long follow-up will be conducted. The primary outcome will be the change in amount of urine leakage at the sixth week from a baseline measured by a 1-h pad test. The secondary outcomes include: the 72-h incontinence episode frequency based on a 72-h bladder diary; the score of International Consultation on Incontinence Questionnaire-Urinary Incontinence Short Form; the degree of urinary incontinence based on a 72-h bladder diary; self-assessment of the therapeutic effect; weekly consumption of pads; application of other treatments for stress urinary incontinence; and subgroup analysis stratified by incontinence severity. The safety of electroacupuncture will also be assessed.

**Discussion:**

This trial will help to identify whether electroacupuncture is effective for stress urinary incontinence, and, if so, whether it is a therapeutic effect rather than a placebo effect.

**Trial Registration:**

Clinical Trials.gov NCT01784172

## Background

Stress urinary incontinence (SUI), defined as the involuntary leakage of urine on effort or exertion, or on sneezing or coughing [1], is a common complaint among adult women. It is generally considered that urinary incontinence (UI) is a prevalent cross-cultural healthcare problem. The global median prevalence of female UI was found to be 27.6% (range: 4.8-58.4%) [2], among which SUI accounted for about 50% [2,3]. Prevalence of SUI increases with age, and a global annual incidence of 4% to 10% was estimated in longitudinal studies [4]. SUI affects not only a patient’s physical health but also her social and psychological wellbeing. Patients are more likely to become depressed and are more prone to self-abasement than other women because of the uncontrollable leakage of urine. This makes them nervous about taking long journeys or participating in social activities. These negative quality-of-life effects are greater than those resulting from some major chronic conditions (diabetes, hyperlipidemia, and chronic kidney disease) [5].

The International Consultation on Urological Diseases (ICUD) recommends lifestyle regulation, behavior therapy, pelvic floor muscle training (PFMT), and functional electrical stimulation as conventional therapies for mild and moderate female SUI. A systematic review supported PFMT as a conservative grade-A recommended therapy for female SUI with a 30-60% effective rate; however, for it to be maximally effective it needs to be practiced for at least 3 months [6]. Additionally, the positive effects of PFMT are closely related with patient compliance [7], which decreases with the extension of training time. PFMT is seldom used in China since skilled physiotherapists are rare. For moderate to severe SUI, a mid urethral sling with surgical mesh is widely used. However, the use of surgical mesh increases adverse events such as pain, infection, dysuria, and neuromuscular problems. A safety communication from the U.S. Food and Drug Administration (FDA) on serious complications associated with transvaginal placement of surgical mesh for pelvic organ prolapse was issued on 13 July 2011 [8]. Several randomized controlled trials (RCTs) showed that acupuncture, by decreasing urine leakage and improving patients’ quality of life, maybe an alternative therapy for SUI [9,10]. However, because of the limited evidence [11], high-quality RCTs are needed to assess the efficacy of acupuncture for treating SUI.

We have designed a multicenter RCT on pure SUI patients that do not exhibit symptoms suggestive of overactive bladder or voiding dysfunction [12]. Using sham electroacupuncture (EA) as control, the trial aims to identify the efficacy of EA by answering two questions: (1) Is EA effective for women with pure SUI? and (2) If effective, is it a therapeutic effect rather than a placebo effect? Additionally, we intend to establish the safety and acceptance of EA in women with pure SUI. The study is registered with a Clinical Trials.gov identifier NCT01784172.

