## Methods

### Study design

This is a multicenter subject-blinded randomized controlled trial comparing EA with sham EA. Five hundred women with pure SUI will be recruited from the following 12 hospitals in China: Guang’an men Hospital of China Academy of Chinese Medical Sciences (CACMS); Xiyuan Hospital of CACMS; Dongzhimen Hospital affiliated to Beijing University of Chinese Medicine; Yueyang Hospital of Integrated Traditional Chinese and Western Medicine affiliated to Shanghai University of Traditional Chinese Medicine (TCM); West China Hospital of Sichuan University; First Teaching Hospital of Tianjin University of TCM; First Hospital of Hunan University of Chinese Medicine; Hengyang Hospital affiliated to Hunan University of Chinese Medicine; Hubei Provincial Hospital of TCM; Jiangsu Province Hospital of TCM;, Shanxi Province Hospital of TCM; and Shanxi Hospital of Integrated Traditional and Western Medicine. Participants will be randomly assigned (on a 1:1 ratio) to the EA group or the sham EA group by a central randomization system performed by the Clinical Evaluation Center of the CACMS in Beijing. The randomization sequence will be generated by the ‘proc plan’ procedure of the SAS9.3 analytic software according to center-stratified, block randomization with a block size of six. Random number and group assignment will be offered by telephone, mobile phone, or website from the Clinical Evaluation Center of the CACMS. In this study, participants, outcome assessors, and statisticians will be blinded to treatment allocation. The flowchart and study design schedule are presented in Figure 1 and Table 1, respectively.

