### Statistical methods

#### Sample size calculation

We conducted a pilot study comparing the effects of deep EA with shallow EA on women with SUI in Guang’an men Hospital of CACMS between June 2011 and February 2012. Results from our pilot study revealed that: compared with the baseline, the volume of urine leakage from the 1-h pad test decreased by 2.10 g, with a standard deviation of 2.26, after 4 weeks deep EA treatment, and by 0.64 g with a standard deviation of 0.97 after 4 weeks shallow EA treatment [16]. We performed sample size calculation according to results of our pilot study because no placebo control trial has been reported. A sample size of 117 in each group will be sufficient to detect a clinically important difference of 1 g on the volume of urine leakage from a 1-h pad test, assuming a standard deviation of 2.61 (considering a larger variability in multicenter trial, the pooled standard deviation of pilot study 1.74 was expanded by 1.5 times), using a one-tailed *t*-test of the difference between means, a significance level of 5%, and a power of 90%. The calculation is based on the assumption that measurements on volume of urine leakage from a 1-h pad test are normally distributed. This number has been increased to 140 per group (total of 280), to allow for a predicted drop-out rate of 20%. As our pilot study had a small sample size (*n*=40) and as we will undertake subgroup analysis, we expanded the sample size to 500 cases (250 cases in each group) to enhance the reliability of the study.

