#### Statistical analysis

Statistical analysis will be performed by the Clinical Evaluation Center of CACMS in Beijing and the Department of Biostatistics, University of Washington, Seattle, United States. The statistician will be blinded from the allocation of groups. PASW Statistics 20.0 and SAS9.0 statistical software will be used for data analysis. The level of significance is established at α<0.05 with a two-tailed test.

The main objective is to compare the change in the amount of urine leakage at week 6 from the baseline between the treatment group and the control group. The null hypothesis is that the treatment group has the same change as the control group, while the alternative hypothesis is that the treatment group shows a greater decrease.

Continuous data will be represented by the average, standard deviation, median, minimum value, and maximum value, whereas categorical data will be represented by percentages. For comparison with the baseline, a *t*-test or non-parametric test will be used for continuous data, and non-parametric tests for categorical data. For comparison of two independent samples: if the residual are normally distributed, the analysis of covariance (ANCOVA) will be used for the primary outcome and subgroup analysis stratified by incontinence severity, a *t*-test for other continuous data, and a chi-square test for categorical data; if the residual are abnormally distributed, a non-parametric test will be used for both continuous and categorical date. Detailed contents and methods are as follows.

1. Case distribution and compliance analysis: The case distribution of both groups in every center will be described. The total drop-out rate and the drop-out rate due to adverse events, of both groups, will be compared using Fisher’s exact test.

2. Analysis of baseline characteristics.

3. Analysis of compliance: The implementation of protocol intervention will be compared between the two groups. Compliance will be evaluated according to the case report forms.

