4. Analysis of efficiency: Intention-to-treat (ITT) analysis will be used to assess the validity of the study. Efficiency analysis will be based on the ITT population which is defined as all randomized participants. Missing data and non-compliance data will be included in the efficiency analysis. Missing data, from subjects without any treatment after randomization, or without any valid data of evaluation although treated, will be analyzed by multiple imputation by the inverse probability weighting method. Non-compliance data will be analyzed by the instrumental variable.

5. Analysis of primary outcome: In this study, we will use the change in the amount of urine leakage at week 6 from the baseline as the primary outcome. To adjust for baseline imbalance, a comparison of the decreased value of urine leakage between the groups will be done by ANCOVA using baseline and centers as covariates, when the residual are normally distributed. Meanwhile, a covariance model including interactions between centers and group will be made to analyze the center effect. Causes will be further analyzed if any center effect is identified. Comparison of decreased value of urine leakage between groups will be analyzed by a non-parametric test if the residual are abnormally distributed with neglect of baseline balance.

6. Analysis of secondary outcomes:

A 72-h incontinence episode frequency (IEF), the International Consultation on Incontinence Questionnaire-Urinary Incontinence (ICIQ-UI) Short Form score, and weekly consumption of pads of weeks 6, 18, and 30 will be compared with their respective baselines, and a *t*-test or non-parametric test will be used for comparison among groups.

For severity of urinary incontinence based on a 72-h bladder diary and a self-report assessment of therapeutic effect, the case number and percentage of each rank of weeks 6, 18, and 30 will be compared with their baselines, and a chi-square test or non-parametric test will be used for comparison among groups.

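### The aims ask whether EA is effective separately from whether it beats placebo; if EA does not beat sham, only uncontrolled tests against baseline remain to call it effective

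*Protocol article*

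**What the plan says.** The Background introduces the aims with "Using sham electroacupuncture (EA) as control, the trial aims to identify the efficacy of EA by answering two questions". The questions are "1) Is EA effective for women with pure SUI? and (2) If effective, is it a therapeutic effect rather than a placebo effect". The Discussion part of the Abstract and the closing paragraph of the Discussion repeat the same two steps. The design has two arms: "This is a multicenter subject-blinded randomized controlled trial comparing EA with sham EA".

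Under Statistical analysis, the main objective, the null and alternative hypotheses and the primary ANCOVA (item 5) all compare the two groups. The same section also plans tests of change from baseline. In general these are a t-test or "non-parametric test will be used for continuous data, and non-parametric tests for categorical data". Item 6 then names outcomes. Episode frequency, the ICIQ-UI Short Form and pad use at weeks 6, 18 and 30 "will be compared with their respective baselines". For severity and the self-report of therapeutic effect, "the case number and percentage of each rank of weeks 6, 18, and 30 will be compared with their baselines". None of these tests is labelled descriptive.

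Table 1 has no W0 mark for the self-report. Table 2 gives its scale as four grades from 'no help' to 'great help'.

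**The concern.** The second question is conditional on a yes to the first, so the wording allows the answer 'EA is effective, but the effect is placebo'. The second question is plainly the sham comparison. If the first is to mean anything different, it has no concurrent comparator.

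The only other planned analyses that could speak to it are the tests against baseline. A fall from baseline can come from treatment, from the natural course of the condition or from non-specific response. It can also come from regression to the mean: a pad gain above 1 g is one route to entry under Participants, and Table 1 schedules one pre-treatment pad test.

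What is at stake is how a null result would be reported. EA could equal sham and still be called effective on a pre-post p-value.

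**Working it through.** **Inputs.** All come from Sample size calculation unless noted.
- Planning SD of change: 2.61 g (1.5 × 1.74).
- Pilot comparator: leakage fell "by 0.64 g with a standard deviation of 0.97 after 4 weeks shallow EA treatment".
- Clinically important difference: 1 g.
- Per arm: 250 women, or 250 × 0.8 = 200 after the predicted 20% drop-out.
- Test level for analysis: two-tailed 5% (Statistical analysis).

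**1. Reproducing the plan's own figure.** Pooled pilot SD = √[(2.26² + 0.97²)/2] = 1.74, and 1.5 × 1.74 = 2.61. One-tailed 5%, 90% power: n = 2 × (1.645 + 1.282)² × 2.61² / 1² ≈ 117 per group. This matches the protocol, so the inputs are read correctly.

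**2. Within-arm test in the control arm.** The test statistic centres on (mean fall) / (SD/√n). Power is taken from the noncentral t distribution with n − 1 degrees of freedom, two-sided 5%.
- n = 250: 2.61/√250 = 0.165, and 0.64/0.165 = 3.88, so power is 97.1%.
- n = 200: 2.61/√200 = 0.185, and 0.64/0.185 = 3.47, so power is 93.2%.

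**3. Sensitivity.** The protocol gives no change for its own sham, so 0.64 g is an assumption. The smaller falls below are assumed values. SD 1.455 is 1.5 × 0.97, the shallow-EA SD inflated by the plan's own factor.

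| Assumed fall in sham arm | SD 2.61, n = 250 / 200 | SD 1.455, n = 250 / 200 |
|---|---|---|
| 0.64 g | 97% / 93% | >99.9% / >99.9% |
| 0.50 g | 85% / 77% | >99% / >99% |
| 0.32 g | 49% / 41% | 93% / 87% |
| 0.20 g | 23% / 19% | 58% / 49% |

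**4. Smallest observed fall that reaches significance at SD 2.61.** 1.96 × 0.165 = 0.32 g (n = 250) and 1.96 × 0.185 = 0.36 g (n = 200). That is about a third of the difference the protocol calls clinically important.

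**5. The controlled comparison.** For a 1 g difference at SD 2.61, the two-sided EA-versus-sham test has 99.0% power at 250 per arm and 96.9% at 200. Resting efficacy on this contrast alone costs nothing in power.

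**6. Self-report item.** Item 6 compares its grades with baseline. Table 1 has no baseline assessment, and a scale of how much treatment has helped has no value before treatment. The comparison cannot be run.

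**The case against.** A reader might infer that the first question can be answered only by the tests against baseline. The documents do not support that. The lead-in names sham as the control for both questions. The only formal hypotheses are between groups, and the Discussion makes confirmation of efficacy depend on EA outperforming the control. Nothing assigns the tests against baseline to question 1, and no decision rule attaches to them. A win over sham answers both questions. This objection stands, and it confines the problem to the case where EA does not beat sham.

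A reader might also infer that the sham arm would very likely be declared improved. That depends on carrying 0.64 g over from four weeks of shallow EA in a pilot of 40 women to six weeks of non-penetrating needling without current. The sample size section itself says no placebo-controlled trial had been reported. This also stands: the 93–97% is an illustration, not a prediction.

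Two smaller points are fair. Item 5 names no baseline test for the pad test, so the illustration relies on the general sentence about continuous data; the pad test is the only outcome for which the document gives figures. The entry criterion also accepts visible leakage instead of a pad gain, and the document does not say whether the W0 test also decides eligibility. Regression to the mean is therefore possible but cannot be sized.

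None of this gives question 1 a controlled answer when EA and sham do not differ, or supplies the missing baseline for the self-report.

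**Conclusion.** The point holds as a fault in how the aims are framed and how the within-arm tests may be interpreted. The primary analysis and its conclusion are unaffected. If EA is not superior to sham, the plan leaves uncontrolled pre-post tests as the only route to calling EA effective, and a two-arm design cannot establish 'effective, but placebo'.

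The size depends on the unknown sham response. At SD 2.61 and 200–250 women, the chance of a significant fall in the control arm runs from 19–23% (true fall 0.20 g) through 41–49% (0.32 g) to 93–97% (0.64 g). It is higher if the SD is smaller. Every value is well above 5%, for an arm meant to have no specific effect.

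The self-report comparison with baseline is wrong as written, and needs no assumption to show it.

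**What to change.** - In the Background, and where the Abstract and Discussion repeat the aims, state one efficacy question: EA versus sham, answered only by the between-group comparison.
- In Statistical analysis, replace the significance tests against baseline with within-arm mean changes and confidence intervals. Label them descriptive and state that no efficacy conclusion will be drawn from them.
- In item 6, delete the baseline comparison for the self-report of therapeutic effect and keep the between-arm comparison already planned there.

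The cost is wording, and there will be no pre-post p-values to report. The primary analysis and the sample size do not change.

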## Methods

### Study design

This is a multicenter subject-blinded randomized controlled trial comparing EA with sham EA. Five hundred women with pure SUI will be recruited from the following 12 hospitals in China: Guang’an men Hospital of China Academy of Chinese Medical Sciences (CACMS); Xiyuan Hospital of CACMS; Dongzhimen Hospital affiliated to Beijing University of Chinese Medicine; Yueyang Hospital of Integrated Traditional Chinese and Western Medicine affiliated to Shanghai University of Traditional Chinese Medicine (TCM); West China Hospital of Sichuan University; First Teaching Hospital of Tianjin University of TCM; First Hospital of Hunan University of Chinese Medicine; Hengyang Hospital affiliated to Hunan University of Chinese Medicine; Hubei Provincial Hospital of TCM; Jiangsu Province Hospital of TCM;, Shanxi Province Hospital of TCM; and Shanxi Hospital of Integrated Traditional and Western Medicine. Participants will be randomly assigned (on a 1:1 ratio) to the EA group or the sham EA group by a central randomization system performed by the Clinical Evaluation Center of the CACMS in Beijing. The randomization sequence will be generated by the ‘proc plan’ procedure of the SAS9.3 analytic software according to center-stratified, block randomization with a block size of six. Random number and group assignment will be offered by telephone, mobile phone, or website from the Clinical Evaluation Center of the CACMS. In this study, participants, outcome assessors, and statisticians will be blinded to treatment allocation. The flowchart and study design schedule are presented in Figure 1 and Table 1, respectively.

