### Participants

The trial plans to recruit 500 women with pure SUI using research nurses or students majoring in acupuncture to do the recruiting.

Inclusion criteria are: (1) aged 40–75 years; (2) involuntary leakage of urine on effort, exertion, sneezing or coughing that stops when the stress ends [13]; (3) visible involuntary leakage from the urethra synchronous with increased abdominal pressure, or a pad weight gain >1 g in a 1-h pad test [13]; (4) no symptoms of urinary frequency and urgency; and (5) voluntarily join the research and sign the informed consent.

Exclusion criteria are: (1) urge urinary incontinence, mixed urinary incontinence, or overflow urinary incontinence; (2) having ever undergone an operation for urinary incontinence or on the pelvic floor; (3) female genital prolapse greater than degree 2; (4) symptomatic urinary tract infection; (5) residual urinary volume (RUV) > 30 mL; (6) maximum flow rate (Qmax) ≤20 mL/s; (7) limited in walking, stairs climbing and running; (8) receiving specific treatment for SUI, or taking medicine that may affect bladder function; (9) serious cardiovascular, cerebral, liver, kidney, or psychiatric disease, diabetes, multiple system atrophy, injury of cauda equina, or myeleterosis; (10) pregnancy or lactation; and (11) having a cardiac pacemaker, a metal allergy, or a severe needle phobia.

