#### Control group (sham EA)

Sham points, which are 1 cun lateral to BL33 and BL35, will be used to match each real point. Sham BL33 and BL35 will be needled through adhesive pads to the skin (for the fixation of needles) without penetrating the skin using blunt needles 0.30 mm in diameter, 25 mm in length (Hwato Brand, Suzhou Medical Appliance Factory, China). The needles will then be lifted, thrust, and twirled evenly three times to match the procedure undertaken for the treatment group. The sham electrode lines (Additional file 5), which look identical to the real ones but with the inner metal wire cut off, will be applied to bilateral sham BL33 and bilateral sham BL35, respectively, and a continuous wave of 50 Hz frequency and an intensity of 5 mA will be applied. When turned on, electric acupuncture apparatus looks normal but has no current output. The intervention of the control group is shown in Additional file 6.

For both groups, the needles will be retained for 30 min for each treatment session. The participants will be treated with EA three times a week, on alternate days, for six successive weeks; 18 sessions for each patient in total.

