## Trial status

This trial is currently recruiting participants, and will be completed by 31 December 2014.

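### A single fixed, printed block size of six within each centre lets anyone holding that centre's ordered allocation record determine a quarter of assignments with certainty

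*Protocol article*

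**What the plan says.** All references are to the protocol article.

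- **Study design** gives the method as "center-stratified, block randomization with a block size of six". No second size is mentioned. On the ratio: "Participants will be randomly assigned (on a 1:1 ratio) to the EA group or the sham EA group". On the strata: "Five hundred women with pure SUI will be recruited from the following 12 hospitals in China". A central system releases each assignment by telephone, mobile phone or website.
- **Study design** also says who is blinded: "participants, outcome assessors, and statisticians will be blinded to treatment allocation". Acupuncturists and recruiters are not named.
- **Treatment group** and **Control group (sham EA)** describe procedures that the operator cannot confuse. The active arm has 75 mm needles inserted 50–60 mm deep. The sham points are treated "without penetrating the skin using blunt needles 0.30 mm in diameter, 25 mm in length".
- **Participants** plans recruitment "using research nurses or students majoring in acupuncture to do the recruiting", while **Interventions** gives treatment to registered acupuncturists.
- **Statistical analysis**, item 5, compares the primary outcome by ANCOVA with baseline leakage and centre as covariates if residuals are normal. Otherwise it uses a non-parametric test that ignores baseline balance.
- **Trial status**: "This trial is currently recruiting participants", with completion by 31 December 2014.

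**The concern.** With one block size throughout, each run of six at a centre must contain three of each arm. Stratification by centre means block boundaries can be found by counting from that centre's first participant, with no information from elsewhere. Whoever has seen the earlier treatments knows the remaining assignments once three of one arm have been used. Central release protects the list itself, but not against deduction from treatments already given.

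What is at stake is the comparability of the arms at entry. Some eligibility items leave discretion, notably visible leakage and the absence of frequency and urgency symptoms, and the timing of entry can also be shifted. If a person with that discretion knew the next assignment, women could be enrolled, deferred or passed over according to arm. Blinding participants and assessors would not correct this, because it acts before treatment starts.

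**Working it through.** **Inputs.** Block size 6, ratio 1:1 and 12 centres (Study design); total 500 (Sample size calculation). Equal recruitment by centre is an assumption: 500/12 = 41.7, about 42 per centre, or 42/6 = 7 blocks. The document states no predictability figure, so there is none to reproduce.

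**1. Certain assignments, fixed block of six.** There are C(6,3) = 20 equally likely sequences. An assignment is certain once one arm's three places are used up.

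| Certain assignments in the block | Sequences | Product |
|---|---|---|
| 1 | 12 | 12 |
| 2 | 6 | 12 |
| 3 | 2 | 6 |
| Total | 20 | 30 |

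Mean = 30/20 = 1.5 per block, and 1.5/6 = 25%. The closed form for a block of 2m agrees: 2m/(m+1) = 6/4 = 1.5 for m = 3. Over the trial this is 0.25 × 500 = 125, or about 10 per centre of 42. Unfinished final blocks would lower it slightly, hence up to about 125.

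**2. Best guess, fixed block of six.** Guessing the arm that is behind gives m + (4^m / C(2m,m) − 1)/2 correct per block. For m = 3: 3 + (64/20 − 1)/2 = 4.1, and 4.1/6 = 68.3%, against 50% by chance.

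**3. The same quantities with varied sizes.** Certain assignments were simulated for 2,000 centres of 42 participants. The observer knew the set of possible sizes and updated after each allocation.

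| Scheme | Certain assignments | Best guess correct |
|---|---|---|
| Fixed 6 (exact) | 25% | 68.3% |
| Fixed 6 (simulated, as a check) | 24.9% | 68.3% |
| 4 and 6 at random | 5.6% | 69.0% |
| 4, 6 and 8 at random | 2.2% | 67.6% |

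The formula in step 2 confirms the last column. It gives 2.83, 4.10 and 5.33 correct for blocks of 4, 6 and 8, so an equal mix of the three yields 12.26/18 = 68.1%.

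**4. Gain from a mid-trial change.** The document does not say how many blocks remain, so let f be the share of the 500 not yet allocated (an assumption). The change removes about 500 × f × (0.25 − 0.022) = 114 × f certain assignments: about 29, 57 and 86 for f = 0.25, 0.50 and 0.75.

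**The case against.** The case on the other side is substantial, and much of it stands.

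- **Who knows and who enrols.** A reader might infer that a quarter of assignments are in fact predictable to recruiters. The document does not support that. The 25% requires a complete ordered record, and recruiting and treating are given to different roles. No statement says recruiters see past allocations. A condensed article may leave the separation of roles to the full protocol, so its silence is not a fault.
- **The best-guess rate.** It is tempting to cite 68.3% as harm from the printed size. Guessing the arm that is behind needs no knowledge of block size, and the rate barely moves when sizes vary. Only the certain assignments depend on the fixed size.
- **Timing.** Table 1 places eligibility and consent a week before the baseline tests. If allocation follows baseline (the flow chart is not shown), a recruiter would have to foresee the block position. This narrows the route, but it leaves the timing of entry open.
- **Eligibility.** The pad criterion is a measured gain above 1 g, and residual volume, flow rate and previous surgery are also explicit. Discretion is limited to a few items.
- **Adjustment.** ANCOVA on baseline leakage and centre addresses steering by measured severity. It does not reach unmeasured prognosis, and the non-parametric fallback drops it.
- **Publication.** Recruitment was open when the article was written, but no publication date is given. Completion on 31 December 2014 less 30 weeks (210 days) puts the last entry at about 4 June 2014, so the window for a change is limited. A size already in print cannot be withdrawn.

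What remains is the stated choice itself: one fixed size, in print, with operators who necessarily know the allocations.

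**Conclusion.** The point holds as a conditional weakness in the randomization design. It is neither an internal contradiction nor evidence of bias. For someone with the block size and the full ordered allocation record of a centre, 25% of assignments are certain on average, up to about 125 of 500. The figure is exact as an expectation for complete 3:3 blocks. Harm further requires that this knowledge reach, and be used by, those who recruit or time entry. The document neither says that this happens nor rules it out. To infer that enrolment was manipulated or that the primary comparison is biased would go beyond the text. Because most of the certainty can be removed cheaply, the change is worth making if unstarted blocks remain.

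**What to change.** Let blocks already open run to completion. For blocks not yet started, have the central system regenerate the list with block sizes varied at random within centre (for example 4, 6 and 8), keeping 1:1 allocation and centre stratification. Withhold the new sizes from all site staff, and publish them only after recruitment ends. Record the change and its date.

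State the gain as a fall in certain assignments from 25% to about 2% in the affected blocks (about 6% with sizes 4 and 6 only). Claim no improvement in the overall best-guess rate, which stays near 68%.

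The cost is one rerun of the unused part of the list and a slightly larger possible within-centre imbalance when recruitment stops partway through a block. Sample size and analysis are unchanged.
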